## 3.2 Secondary Endpoint Parameters

- Mechanical complication occurrence due to ETT cuff over inflation will be evaluated by the following measures during the 48h post extubation:
  - Throat pain level, associated with the mechanical ventilation. Pain level will be assessed by VAS (visual analogue scale) questionnaire;
  - Hoarseness occurrence
  - Spirometry analysis
  - Fiber optic analysis (this measure will be used in selected ICUs)
- Medical staff satisfaction from AnapnoGuard 100 system operations and performance will be established by designated questionnaire for physicians and nurses.

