**Time Table**

|  | **Screening** | **Connection to AnapnoGuard System** | **Mechanically Ventilation**  **Period** | **After AnapnoGuard Disconnection** | **Post Clearance Follow-up Phone Information** |
| --- | --- | --- | --- | --- | --- |
| **Time line** | **During hospitalization in ICU** | **Up to 6 h from intubation initiation** | **Daily evaluation** | **48h post extubation** | **1 month following extubation** |
| **Informed consent** | x |  |  |  |  |
| **Inclusion criteria** | x |  |  |  |  |
| **Medical history** | x |  |  |  |  |
| **Chest x-ray** | x | X | x* | x |  |
| **Blood tests** | x | X | x | x |  |
| **Vital signs** | x | X | x | x |  |
| **Trap bottle secretions***** |  |  | x |  |  |
| **Oxygen saturation** | x | x | x | x |  |
| **Mechanical complication assessment**** |  |  |  | x |  |
| **Subject’s general condition** |  |  | x | x | x |
| **AE and SAE** |  | x | x | x |  |
| **Study deviation** |  | x | x | x |  |
| **Final statistical analysis** |  |  |  | x |  |
| **Study exit** |  |  |  | x |  |

* Chest X-ray will be done at baseline, 48 hours after intubation and whenever there is clinical suspicion for VAP

** Mechanical complications assessment will include: spirometry, fiber optic in selected ICUs and questionnaire regarding throat pain and hoarseness.

***Recording level of trap bottle secretions 3 times a day (per shift). Records – Images and or electronic record

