**Study Synopsis**

| **Study title** | **The safety of using AnapnoGuard 100 in intubated critical Care patients** |
| --- | --- |
| **Study number** | Protocol # **HST- AG­– 04**;Version 1.1 |
| **Sponsor** | Hospitech Respiration Ltd. |
| **Study design** | Prospective, single - center, double-arm, randomized-controlled open label, safety study. |
| **Recruitment duration** | Estimated recruitment duration: approximately 12 months. Study duration for each subject depends upon mechanical ventilation duration, which will be defined by subject’s general condition. |
| **Study site** | The study will be conducted at the ICU of the Università Cattolica del Sacro A Gemelli University Hospital, Rome, Italy. in Rome. Additional ICU may be added. |
| **Principal Investigator** | Professor [name], Director of the institute of Anaesthesiology and Intensive care. |
| **Investigational product** | Intended Use/Indications for Use:  ***AnapnoGuard™ 100 Respiratory Guard*** Systemis intended for airway management by oral/nasal intubation while providing continuous endotracheal cuff pressure control using non-invasive measurement and monitoring of carbon dioxide concentration in the subglottic space and evacuation of secretions from above the endotracheal tube’s cuff.  The system is comprised of the following main three components:   1. AnapnoGuard 100 control unit 2. Single use AnapnoGuard endotracheal tube with two suction lumens and a vent lumen 3. Single use AnapnoGuard interface harness and filters kit |
| **Patient population** | Patient admitted to ICU and expected to receive mechanical ventilation for at least 12 hours. Patient will be randomly assigned to study or control group using the block randomization method. |

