# STUDY OBJECTIVES AND PURPOSE

## 2.1 Clinical Trial Design

This study is a Prospective, Single - center, Double-arm, Randomized-controlled Open label, safety study.

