  - ~~Prior to participation in the trial,~~ the subject's legally acceptable representative should receive a copy of the signed and dated written ICF and any other written information provided to the subjects. During a subject’s participation in the trial, the subject’s legally acceptable representative should receive a copy of the signed and dated consent form updates and a copy of any amendments to the written information provided to subjects.
  - Subject's legally acceptable representative must provide informed consent and sign and date with his hand writing an ICF prior to any study related procedures being performed. The person reviewing the ICF with the subject must also sign and date the ICF. Each of the signers must sign and date in the presence of the other signer.
  - Allocated informed consent study staff will make efforts to obtain written informed consent prior to enrollment (for study patients – Before connection to the AnapnoGuard 100 system and for control patients - as soon as possible following intubation). Nevertheless, for specific cases (e.g. patients arriving at the ICU without an accompanying legal representative, there will be a 24 hour window to achieve written informed consent. The reason for enabling a 24 hour window for written ICF in the control group has to do with the fact that these patients will be treated with conventional standard of care. A 24 hour written ICF is allowed for the study group as well as for the control group since the investigational device, the AnapnoGuard 100 respiratory system, is a commercially (CE Mark) available device that is intended for non-life supporting functions and performs the following two basic operations; cuff pressure control and suctioning above the cuff.

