# 7. DeVICE MAINTENENCE AND DISPOSAL

The AnapnoGuard endotracheal tube ETT and the connection kit are sterile, singe use components, which need to be properly disposed after extubation.

The AnapnoGuard 100 system should be disinfected and cleaned after each patient according to Hospitech Respiration LTD instructions.

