## Investigator's Obligations

Clinical research studies are subject to the regulations of the local Health Authority. Upon signing the protocol, the Investigator agrees to assume the following responsibilities and to keep the required records for a period of three years following completion of the study and to file the required reports in a timely manner:

1. Conduct the Investigation in compliance with the protocol. Changes to the protocol may only be made after approval by the Sponsor, or when necessary to protect the safety, rights or welfare of a subject.
2. Personally conduct or supervise the investigation.
3. Read and understand the information in the Protocol and Investigator Brochure.
4. Be aware of the potential risks and side effects of implanting the AnapnoGuard system.
5. Ensure that all associates, colleagues and employees assisting in the conduct of the study are qualified, properly trained on the use of the device and are informed about their responsibilities and obligations related to the study.
6. Inform all subjects that the device is being used for investigational purposes and ensure that the requirements related to obtaining the informed Consent are met.
7. Screen patients and enroll to the study only patients who meet the inclusion criteria.
8. Dispose of remaining supplies as directed by the Sponsor.

Maintain the following records (for a period of three years following completion of the study):

1. Signed copy of the protocol.
2. Signed Inform Consent forms.
3. All correspondence as relates to the clinical trial.
4. Case Report Forms.

File the following reports:

1. Severe Adverse Events must be reported to the sponsor by phone within 24 hours. A written report must follow within five (5) working days.
2. Unanticipated adverse device related effects must be reported to the sponsor as soon as possible, within 10 working days.
3. Deviations, which were made from the protocol for emergency use, must be reported to the sponsor as soon as possible, but no later than five (5) working days after its occurrence.

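### Nothing keeps the arm from the patient or the assessor for throat pain and hoarseness, so these post-extubation measures are open to an expectation bias that a low-cost rule could reduce

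*Protocol*

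**What the plan says.** - **Masking.** Section 2.1 calls the trial a "Prospective, Single - center, Double-arm, Randomized-controlled Open label, safety study", and the Study Synopsis agrees. No section makes an exception for any outcome.
- **Outcomes.** Section 3.2 measures mechanical complications of cuff over-inflation by "Throat pain level, associated with the mechanical ventilation. Pain level will be assessed by VAS (visual analogue scale) questionnaire", by hoarseness occurrence, by spirometry and, in selected ICUs, by fibre-optic examination. These "will be evaluated by the following measures during the 48h post extubation". Section 6.8 repeats the list.
- **Instrument.** The Time Table footnote refers to a "questionnaire regarding throat pain and hoarseness". Neither it nor sections 3.2 and 6.8 say who completes or administers it.
- **Equipment.** Section 7 describes the tube and connection kit as single-use items "which need to be properly disposed after extubation".
- **Consent.** The legally acceptable representative consents. Under section 6.1 this is sought "for study patients – Before connection to the AnapnoGuard 100 system and for control patients - as soon as possible following intubation", with a 24 h window in specific cases.
- **Information to the subject.** Section 13.2 (Investigator's Obligations), item 6, tells the investigator to "Inform all subjects that the device is being used for investigational purposes". It does not mention the arm and sets no timing relative to the questionnaire.
- **Analysis.** Section 8.4 states descriptive statistics only. The one hypothesis, in section 8.3, compares the success proportion on the study device with 0.80.

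**The concern.** An open label is hard to avoid for bedside staff while the system is running. It is less necessary for what the patient reports afterwards. The patient has been ventilated, someone else gave consent, and the tube and kit are gone. Whether the patient knows the arm may then depend largely on what staff or relatives say, and the Protocol gives them no instruction.

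Throat pain and hoarseness are self-perceived symptoms. The device is presented in the clinical background (section 1) as using the minimal cuff pressure needed to prevent a leak. A patient told that this device was used, or a staff member asking the questions with that in mind, could shift the answers. With about 25 patients per arm, such a shift could be read as less over-inflation injury. Section 9.3 also lists the same symptoms as potential adverse events and section 8.1 tabulates adverse events by arm, so a shift could reach those tables too.

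Who is told the arm, and when, is a matter of trial conduct. A statistical analysis plan cannot repair it once the answers have been collected.

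**Working it through.** **Step 1. Is masking feasible in the window?** Set the sections side by side.

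- Assessment falls within 48 h after extubation (3.2, 6.8); the tube and kit are discarded after extubation (7). The equipment need not disclose the arm at the time of asking.
- The Time Table marks only general condition at the 1-month phone contact. Withholding the arm until the questionnaire is done, at most 48 h, therefore covers the whole window for these outcomes.
- Item 6 of 13.2 can be met by telling the subject about the trial and the investigational device without naming the arm. The two are compatible, but the wording does not say so.

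**Step 2. Is disclosure shown?** No. No section says that the patient is told the arm, and none prevents it. The supported statement is that the outcomes are open to bias.

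**Step 3. How much could a shift matter?** The Protocol has no figure to reproduce: it gives no SD, no VAS length, no effect size and no between-arm test for these outcomes. The following is an illustration.

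| Input | Value | Source |
| --- | --- | --- |
| Patients per arm, n | 25 | section 8.2 |
| VAS | 0-10 cm | assumed |
| SD | 2.5 cm (range 2-3) | assumed |
| Reporting shift, b | 0.5 or 1 cm, no true effect | assumed |
| Test | two-sided 5%, normal | assumed; not in the Protocol |

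Standard error of the difference in means: SE = SD × √(2/25) = SD × 0.283.

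Chance of an apparent difference with no true effect: P(Z > 1.96 − b/SE) + P(Z < −1.96 − b/SE).

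| SD (cm) | SE (cm) | 95% half-width, 1.96 × SE (cm) | b = 0.5 cm | b = 1 cm |
| --- | --- | --- | --- | --- |
| 2 | 0.566 | 1.11 | 14.3% | 42.4% |
| 2.5 | 0.707 | 1.39 | 10.9% | 29.3% |
| 3 | 0.849 | 1.66 | 9.1% | 21.8% |

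**Step 4. Sensitivity to the number who answer.** With 30 per arm (all 60 enrolled), a shift of 0.2 SD (0.5 cm at SD 2.5) gives 12.1% and one of 0.5 SD (1 cm at SD 2) gives 49.1%. With an assumed 15 completers per arm, SD 2.5 and b = 1 cm, SE = 2.5 × √(2/15) = 0.913 and the rate is about 19%.

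Every shift considered here is smaller than the 95% half-width, so it could not be told apart from sampling noise. It would still move the descriptive estimate by its full amount.

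**The case against.** The strongest reply is that no bias has been demonstrated. A reader might infer from 13.2 item 6 that patients are told their arm before rating the throat. The text does not support this: it requires only that they be told the device is investigational, and it is silent on allocation. The information sheet is not in the text available and may already deal with it. This stands, and it limits the claim to exposure to bias.

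A reader might also take the 22-42% as this trial's error rate. It is not. The Protocol states no between-arm test of these measures, and the SD and shift are assumed. The 0.5 cm shift is below the SE throughout the assumed SD range. Fewer completers would lower the rates, and some attrition is likely because re-intubated patients may be withdrawn (section 4.2).

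It might seem that keeping the arm from the patient settles the matter at no cost. It does neither. The rater of hoarseness is not named; if unmasked staff ask or judge, the exposure remains. An awake patient may have seen the console, and the representative may know the arm. Coding a spirometry tracing does not mask the person coaching the manoeuvre. So the remedy must include self-completion or a questioner not told the arm, and its protection is partial.

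Finally, these measures are secondary and do not decide study success, which under section 3.1 turns on device-related events during intubation. The allocation of ten consecutive patients to one arm in section 4.1 is a separate and larger threat to any between-arm contrast, and this change would not remove it. Both points stand and keep this one minor. They do not remove it: the gap is real and the instruction that closes most of it is short.

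**Conclusion.** The point holds in limited form. The trial is open label, throat pain and hoarseness are subjective, they are collected when the tube and kit are gone, and nothing in the Protocol keeps the arm from the patient or assessor. They are open to expectation bias, but its presence and size cannot be established from the documents. Under the stated assumptions (25 per arm, SD 2-3 cm, a two-sided 5% comparison that the Protocol does not plan), a 0.5 cm shift would give 9-14% and a 1 cm shift 22-42% in place of 5%. This is a minor improvement to the conduct of secondary outcomes, worth making because it is cheap. It has no bearing on the primary success criterion.

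**What to change.** - **Sections 3.2 and 6.8:** state that staff do not tell the subject which tube was used until the throat-pain VAS and hoarseness questionnaire are completed, unless the subject asks or there is a clinical need.
- **Same sections:** have the patient complete the VAS and hoarseness items personally or, where existing staff allow, have them asked by someone not told the arm.
- **CRF:** add an item recording whether the arm was known when the questionnaire was completed.
- **Spirometry and fibre-optic records:** label tracings and images by subject number only.
- **Section 13.2 item 6:** word it so that informing subjects of the investigational status of the device does not require disclosing the arm before the questionnaire. Match the information sheet to it.

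The cost is low but not nil: wording in three sections, a line in the information sheet, one CRF item and an instruction to staff, with no added procedure or staff. The downsides are that disclosure is delayed by up to 48 h after extubation and that masking stays incomplete for patients who saw the console while awake or heard from a relative. The CRF item would show how often that happened.

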**3.3 Other Observations**

- Evaluation of the effect of AnapnoGuard system upon ventilator associated pneumonia (VAP) occurrence rate and time to VAP in intubated patients in intensive care units (ICU)

# 4. Selection and Withdrawal of Subjects

## 4.1Source of Subjects and Enrollment

Male/female subjects admitted to ICU and expected to be mechanically ventilated for at least 12 hours. A minimum of 12 hours of intubation is required due to the fact that the AnapnoGuard 100 system’s intended use is for patients with prolonged ventilation with endotracheal tubes. In order to evaluate the safety of the device, the subject should be intubated for at least 12 hours.

~~Only subjects that their legally acceptable representative have signed an Informed Consent Form and meet all of the eligibility criteria listed below will be qualified for enrollment. Upon recruitment, subjects will be randomized, using the sequentially numbered opaque sealed envelopes (SNOSE) randomization method, to be treated with AnapnoGuard system (Study Group) or to be treated according to the standard ICU procedure (Control Group).~~

Male/female subjects admitted to ICU and expected to be mechanically ventilated for at least 12 hours. Subjects will be randomized to study/control group prior to enrollment in blocks of ten (the first 10 subjects (1-10) will be selected for study group; the second 10 subjects (11-20) will be selected for the control group, and so on). Subjects will be intubated with either Hospitech’s ETT or Covidien’s ETT (10-10) and only after intubation they will be screened. Only subjects that meet all of the eligibility criteria listed below and their legally acceptable representative has signed an Informed Consent Form will be qualified for enrollment.

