### 6.4 Connection to ETT, Operation and Monitoring Procedure

Following enrollment, subjects will be randomized to a study group or control group using the block randomization method. Treatment will be as follows:

- The study group patients will be treated with the AnapnoGuard 100 system and will be intubated with the AnapnoGuard's ETTs.

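### Section 4.1 allocates by fixed alternation, ten study then ten control, before screening and consent, which contradicts the randomised label and Section 6.4

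*Protocol*

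**What the plan says.** The synopsis describes a "Prospective, single - center, double-arm, randomized-controlled open label, safety study" and adds: "Patient will be randomly assigned to study or control group using the block randomization method". Section 2.1 repeats the design label: "This study is a Prospective, Single - center, Double-arm, Randomized-controlled Open label, safety study".

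Only Section 4.1 says how an arm is chosen. It begins "Subjects will be randomized to study/control group prior to enrollment in blocks of ten" and then defines the blocks: "the first 10 subjects (1-10) will be selected for study group; the second 10 subjects (11-20) will be selected for the control group". The pattern continues ("will be selected for the control group, and so on"). Patients are intubated with the tube of their arm, "and only after intubation they will be screened". Meeting the criteria and having the representative's signed consent are conditions of enrolment that come after that. The envelope method in the same section is struck through and is not in force.

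Section 6.4 gives a different order: "Following enrollment, subjects will be randomized to a study group or control group using the block randomization method". It supplies no sequence and no means of concealment. Section 6.3 assigns the sequential subject number during screening.

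**The concern.** In block randomisation the order of arms inside each block is random. Here each block of ten belongs wholly to one arm and the arms alternate by a written rule, so anyone with the protocol knows the next assignment. Eligibility and consent are then decided by staff who can see which tube is in place, in an open-label trial.

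Two things are at stake. First, selection: knowledge of the arm can influence who is intubated during a run, who is judged eligible and whose representative is approached. Second, time: differences in case mix, staffing or practice between periods, and growing experience with the device, become differences between arms. Randomisation is what would normally guard the between-arm comparisons against both.

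**Working it through.** No figure in the protocol needs reproducing for this point. The check writes out the stated sequence, compares it with genuine blocks, and sets the sections side by side.

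**Inputs.** Total of 60 patients (synopsis; Section 8.2). Runs of ten, alternating, starting with the study group (Section 4.1). Recruitment of about 12 months (synopsis; Section 6.2).

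**1. The sequence as written.** 60 / 10 = 6 runs. Study: 1–10, 21–30, 41–50. Control: 11–20, 31–40, 51–60. That is 30 per arm and one possible sequence, so 60/60 = 100% of assignments are known beforehand.

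**2. Benchmark: genuine 5:5 blocks of ten.** Each block has C(10,5) = 252 orders, so six blocks give 252^6, about 2.6 × 10^14 sequences. Take an observer who knows the block size 2m and all past assignments, and always guesses the arm with more places left. The expected number of correct guesses per block is m + (4^m / C(2m,m) − 1)/2.
- Blocks of 10: 5 + (1024/252 − 1)/2 = 6.53 of 10, about 65%.
- Blocks of 6: 3 + (64/20 − 1)/2 = 4.10 of 6, about 68%.
- Blocks of 4: 2 + (16/6 − 1)/2 = 2.83 of 4, about 71%.

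Simulation gave the same values (0.653, 0.683, 0.708).

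**3. Arm and time.** The mean position in the sequence is (5.5 + 25.5 + 45.5)/3 = 25.5 for study and (15.5 + 35.5 + 55.5)/3 = 35.5 for control. Control patients therefore come ten places later on average, 10/60 or one sixth of recruitment. Under genuine 1:1 blocks the expected gap is zero. *If* accrual is even and there is one sequence, each run lasts 12/6 = 2 months, and roughly the first two months are all AnapnoGuard.

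**4. Order of steps.**

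| Section | Order |
| --- | --- |
| 4.1 | allocate, intubate with the arm's tube, screen, consent, enrol |
| 6.3 | check criteria, obtain consent and assign the subject number, all before study-specific procedures |
| 6.4 | enrol, randomise, treat and intubate by arm |

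A site cannot follow all three. Section 4.1 needs the subject's place in the sequence to choose the tube, whereas Section 6.3 issues the number only at screening.

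**5. Room for judgement once the arm is known.** Expected ventilation beyond 12 hours, clear signs of pneumonia on the X-ray and the origin of fever (Section 4.2) all need interpretation. The exclusion for more than three intubation attempts can be observed only while a tube is being placed. Section 6.1 allows written consent up to 24 hours later in specific cases.

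**6. Which analyses depend on allocation.**
- Section 8.3: the AnapnoGuard success proportion is tested against 0.80. No control quantity enters.
- Section 3.1: serious adverse events are to be compared with the control group. This depends on allocation.
- Section 3.3: the effect of the system on VAP occurrence and time to VAP. An effect implies a comparison with control.
- Section 3.2: mechanical complications are to be evaluated. No comparison with control is stated, but any between-arm reading depends on allocation.

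**The case against.** The strongest reply is that the only stated hypothesis and success rule concern one arm. The 25 per group comes from that one-sample test, and the control group simply receives the same number. Section 8.4 plans descriptive statistics and no between-arm test, and VAP is listed under other observations. This stands as far as it goes. A reader might infer that the declared study conclusion is invalid because allocation is not random. The protocol does not support that, because allocation order does not enter the test. What remains is that staff who know the arm while screening could alter which patients make up the tested proportion.

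A reader might also infer that the order in Section 6.4 is unworkable. Read alone it is coherent: enrol, randomise, intubate. It fails only when combined with Section 4.1, so this is a contradiction to reconcile.

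It is also tempting to treat the six runs as clusters and quote a loss of effective sample size. The protocol gives no within-run correlation, and no stated analysis or power statement uses the pooled 60 in that way, so no such figure is justified.

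The two-month run length is conditional too. Section 6.2 makes duration depend on recruitment, the synopsis allows further ICUs, Section 6.3 numbers subjects per site, and Section 4.1 does not say whether patients 1–10 are those intubated or those enrolled. The rule is deterministic under each of these readings.

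**Conclusion.** The point holds. As written, Section 4.1 is fixed alternation in runs of ten, with the arm known before eligibility and consent are decided. It contradicts the design label in the synopsis and Section 2.1, the block-randomisation label in the synopsis and Section 6.4, and the timing in Section 6.4. Predictability is 100%, against about 65% for genuine blocks of ten. Taken as one sequence of 60, control patients come ten places later on average.

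The consequence is limited to the between-arm comparison of serious adverse events, the VAP effect and any between-arm reading of mechanical complications. The formula of the one-sample primary test is untouched. The text shows an opportunity for selection, not that selection will occur, and it gives no basis for a numerical bias. The point still needs correcting before the trial is described as randomised, because an analysis plan cannot restore randomisation or concealment afterwards.

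**What to change.** Replace the ten/ten rule in Section 4.1 with a computer-generated 1:1 permuted-block list. Use varying small blocks (for example 4 and 6), do not disclose the sizes to the site, and conceal each assignment until the decision to intubate. The guessing rates above apply to an observer who knows the size, which is why the sizes should vary and stay undisclosed. Reconcile Sections 4.1, 6.3 and 6.4 to one order, including when the subject number is issued.

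Log every allocation, and report screen failures and refusals after allocation by arm with reasons. This is needed because eligibility and consent are still decided with the arm known. The log makes such selection visible but does not prevent it.

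If the ten/ten rule is kept, describe the study as a non-randomised alternating-cohort design in the synopsis, Sections 2.1, 4.1 and 6.4, and the conclusions. The study title does not claim randomisation and needs no change.

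Cost: a protocol amendment, both tube types at hand for each intubation, and possibly replacement of patients who fail screening or whose representatives refuse after allocation.
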